#### Primary analysis

To address the primary aim, we will compare the rate of returning to the preinjury sport and level at 12 months between the treatment groups. We will calculate the odds ratio and 95% confidence interval using generalised estimating equations. Group and clinical site will be included as fixed factors in the model.

#### Planned secondary analyses: time-varying analyses

We will compare psychological readiness to return to sport (ACL-RSI), motivation to return to sport, self-reported knee function (SANE and IKDC), sports participation and new knee injury between treatment groups using generalised estimating equations. Group, clinical site, and assessment time point will be included as fixed factors. If baseline values were collected, we will also include the baseline value in the relevant model as a covariate. For continuous variables, we will calculate mean difference and 95% confidence intervals. For dichotomous variables, we will calculate the odds ratio and 95% confidence intervals.

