**Methods:**

Participants scheduled for primary ACL reconstruction are recruited prior to surgery from one of six trial sites in Sweden. We aim to recruit 222 participants (111 in each group) for the BANG trial. Participants are randomly allocated to receive either usual rehabilitation care alone or usual rehabilitation care plus the Back in the Game smartphone application intervention. Back in the Game is a 24-week Internet-delivered programme, based on cognitive-behavioural therapy. The primary outcome is return to the preinjury sport and level at 12 months follow-up. The secondary outcomes assess physical activity participation, new knee injuries, psychological factors, quality of life and physical function. Physical activity participation and new injuries are self-reported every two weeks for 12 months, then every 4 weeks to 24 months follow-up. Psychological readiness to return to sport, knee self-efficacy, motivation to participate in leisure time physical activity, knee-related quality of life, and self-reported knee function are also assessed at 3, 6, 9, 12 and 24 months after surgery. A clinical assessment of strength, knee range of motion, effusion and hopping performance is completed by a blinded assessor at 12 months to assess physical function.

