### Outcomes

The primary outcome is the proportion of participants who return to their preinjury sport *and* participation level at 12 months. The secondary outcomes (Table 2, Additional file 1) are measured at clinically-relevant times, and reflect a biopsychosocial approach to outcome evaluation: patient- and clinician-reported knee function, sports participation and new knee injuries for the biological aspect, psychological readiness to return to sport and self-efficacy for the psychological aspect, adherence to the intervention and/or rehabilitation, and a range of baseline characteristics (Table 3, Additional file 1) for the social aspect.

**Table 2 Tab2:** Summary of secondary outcomes

Measurement variable	Aggregation method	Measurement time point(s)
Sports participation	Number of minutes playing (i) contact, pivoting sports, (ii) non-contact, pivoting sports, (iii) non-pivoting sports	Every 2 weeks to 12-months follow-up; every month from 12 to 24 months follow-up
New knee injuries	Proportion of participants who report a new (i) ACL injury, (ii) meniscus injury, (iii) other knee injury or problem	Every 2 weeks to 12-months follow-up; every month from 12 to 24 months follow-up
Psychological readiness to return to sport	Mean or median ACL-Return to Sport after Injury scale [24] score	3, 6, 9, 12, 24 months
Knee-related self-efficacy	Mean or median Knee Self-Efficacy Scale [25] future domain score	12, 24 months
Motivation to return to sport [26]	Median	3, 6, 9 months
Knee-related quality of life	Mean or median ACL-Quality of Life scale [27] score	12, 24 months
Self-reported knee function	Mean or median International Knee Documentation Committee subjective knee form [28] score	6, 12, 24 months
Self-reported knee function	Mean or median Single Assessment Numeric Evaluation [29]	Every 2 weeks to 12-months follow-up; every month from 12 to 24 months follow-up
Functional knee stability	Frequency of giving way episodes	12, 24 months
Knee effusion	Proportion of participants with stroke test [30] score: 0, trace, 1+, 2+, 3+	12 months
Hopping performance [31, 32]	Mean or median limb symmetry index	12 months
Quadriceps and hamstrings strength	Mean or median limb symmetry index	12 months
Adherence to rehabilitation	Number of sessions completed	Every 2 weeks while completing rehabilitation
Adherence to BANG intervention	Number of completed video and audio sessions	6 months

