#### Harms

Participants report any adverse events – an untoward physical or psychological occurrence with or without an expected causal relationship to the intervention (e.g. deep vein thrombosis, embolism, superficial or deep infection to the index knee, psychological distress, increase in knee symptoms, ligament sprain, muscle strain, meniscus tear) to the trial co-ordinator via electronic questionnaire (open-ended question sent every 2 weeks during the first year of follow-up; we expect usual care rehabilitation to have a duration of approximately 9 months). A serious adverse event for this trial is any untoward physical or psychological occurrence that the trial investigators believe is causally related to the intervention *and* is any of the following: life-threatening, associated with permanent and/or severe disability, associated with prolonged hospitalisation. Serious adverse events will be reported to the regional ethics review board.

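### The secondary models headed time-varying have no group-by-time term, so each listed outcome gets one effect pooled over follow-up, and new knee injury is modelled per registration although it is defined per participant

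*Protocol article*

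**What the plan says.** The relevant text is in the protocol article's Statistical analysis plan, under Planned secondary analyses: time-varying analyses. It covers ACL-RSI, motivation, "self-reported knee function (SANE and IKDC), sports participation and new knee injury between treatment groups using generalised estimating equations". The model terms are listed: "Group, clinical site, and assessment time point will be included as fixed factors". The baseline value is added as a covariate where one was collected. The reported quantities carry no time point: "For continuous variables, we will calculate mean difference and 95% confidence intervals" and "For dichotomous variables, we will calculate the odds ratio and 95% confidence intervals".

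Table 2 (Outcomes) gives these measurement times:
- ACL-RSI: 3, 6, 9, 12 and 24 months.
- IKDC: 6, 12 and 24 months.
- Motivation: 3, 6 and 9 months only.
- SANE, sports participation and new knee injuries: "Every 2 weeks to 12-months follow-up; every month from 12 to 24 months follow-up".

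Table 2 defines the injury outcome as "Proportion of participants who report a new (i) ACL injury, (ii) meniscus injury, (iii) other knee injury or problem". Reclassifying variables plans three dichotomous injury variables but does not say whether each is formed per registration or per participant.

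The cross-sectional section that follows fits separate 12- and 24-month models for K-SES and ACL-QoL. The primary analysis is fixed at 12 months.

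**The concern.** A model with group and time point as main effects lets the outcome mean change over follow-up but holds the group difference constant. A section whose heading promises time-varying analyses therefore fixes a treatment effect that cannot vary with time.

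There are two consequences. First, an effect that emerges late is averaged with earlier visits, and an effect that fades by 24 months cannot be told from a smaller constant one. This matters most for sports participation, where usual rehabilitation occupies much of the first year (Harms: "we expect usual care rehabilitation to have a duration of approximately 9 months") and registrations are twice as frequent in that year.

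Second, placing new knee injury in a model indexed by registration makes the registration the unit of analysis, while Table 2 makes it the participant. Issues related to adverse events names re-injury as a possible harm of an app that succeeds in returning athletes to sport, so it should be clear what the injury odds ratio measures.

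**Working it through.** The protocol states no numerical figure for these secondary models, so there is none to reproduce. The check is on what the stated model estimates.

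**1. What the group coefficient is.** With an identity link, complete data, time as a factor and an independence or exchangeable working correlation, the group coefficient is the simple mean of the visit-specific group differences: (d1 + d2 + ... + dK)/K. Missing visits change the weights, but the result is still a single average.

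**2. Number of registrations.** Table 2 gives 26 fortnightly + 12 monthly = 38. The abstract's schedule ("self-reported every two weeks for 12 months, then every 4 weeks to 24 months follow-up") gives 26 + 13 = 39. Year 1 supplies 26/38 = 68% of the records.

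**3. Share before rehabilitation ends.** Harms gives about 9 months. Table 1 (Interventions) gives at least 6 months, usually finished by 12.

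| Rehabilitation ends | Registrations by then | Share of 38 | Share of 39 |
|---|---|---|---|
| 6 months | 13 | 34% | 33% |
| 9 months | 19 | 50% | 49% |
| 12 months | 26 | 68% | 67% |

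**4. Dilution for sports participation.** Assume no effect until rehabilitation ends, a constant effect D afterwards, and equal weights. The pooled coefficient is then D × (1 − share):
- 6 months: 25/38 = 0.66 D
- 9 months: 19/38 = 0.50 D
- 12 months: 12/38 = 0.32 D

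**5. Visit-based scales (illustration only).** If an effect of 1.0 is present at 12 and 24 months and absent before, the average is 2/5 = 0.40 for ACL-RSI and 2/3 = 0.67 for IKDC. A simulated ACL-RSI data set with this pattern and an exchangeable correlation gave 0.41 from the model as written. With group-by-time added, the 12-month contrast was 1.03.

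**6. Fading effect.** If an ACL-RSI effect of 1.0 exists at 12 months only, the pooled value is 1/5 = 0.20. A constant effect of 0.20 at all five visits gives the same value, so the coefficient cannot separate the two.

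**7. Injury.** The time-varying model has one row per participant per registration, so its odds ratio compares the odds of a report at a given registration. Table 2's proportion has one value per participant. Someone who reports new knee problems at three registrations contributes three positive rows to the first and one to the second. For an event that rarely recurs, such as ACL injury, the two odds ratios may be close. For the all-complaints variable they need not be.

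**The case against.** The strongest reply is that a time-averaged difference is a legitimate target. The secondary aims name no time point, averaging gains precision, and a separate analysis plan may specify interactions and contrasts. It is true that the pooled effect contradicts no stated aim. But the article does not leave the point open: it lists the model terms. The neighbouring section shows that the authors name time-specific contrasts when they intend them.

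A second reply is that early data are not noise. The app runs for the first 24 weeks, and Table 1 says its early content targets confidence in recovery. ACL-RSI, SANE, IKDC and motivation could respond early. This stands, so the dilution range is claimed only for sports participation.

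Some stronger readings are not supported:
- *That every secondary result lacks a 12-month estimate.* K-SES and ACL-QoL have one. Effusion, hopping and strength are measured only at 12 months. Motivation has no 12-month value to estimate.
- *That about half is a firm share.* It rests on the 9-month figure alone; the protocol's own range gives 34% to 68%.
- *That early pivoting-sport minutes are known to be near zero.* The document gives no such figure, and Table 2 also counts non-pivoting sport.
- *That the injury model cannot be fitted because some of the 38 time levels would contain no event.* Those are nuisance terms. In trial fits the group coefficient was usually estimable, and the protocol names no working correlation.

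The injury mismatch is also partly an ambiguity, since Reclassifying variables could be read either way.

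**Conclusion.** The point holds for the outcomes listed in the time-varying section. As written, each gets a single time-constant group effect: ACL-RSI over 3 to 24 months, IKDC over 6 to 24, motivation over 3 to 9, and SANE, sports participation and new knee injury over about 38 registrations. None gets a time-specific effect.

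For sports participation the pooled estimate would show about half of a late effect, with a range of roughly a third to two thirds. That rests on equal weighting and on an effect that begins only when rehabilitation ends. Neither is stated in the protocol, and an effect that starts earlier would be diluted less.

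Read literally, the injury analysis gives an odds ratio per registration, which is not the participant proportion in Table 2. The wording should be corrected before analysis. The 12-month primary analysis is not touched.

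**What to change.** 1. Add a group-by-time term to each model in the time-varying section. Report the 12-month contrast first and 24 months second where those visits exist, and the 3-, 6- and 9-month contrasts for motivation. The time-averaged effect can be kept as a supplementary summary.
2. Group the fortnightly and monthly series into longer periods, for example 3 months, so that the interaction has few levels.
3. Analyse each new-injury variable with one row per participant, either as the cumulative proportion by 12 and by 24 months or as time to first report. State the unit in Reclassifying variables as well.

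This changes analysis wording only and uses data already being collected. The cost is that a single-time contrast is somewhat less precise than the pooled average.

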#### Planned secondary analyses: cross sectional analyses

For self-efficacy (K-SES) and quality of life (ACL-QoL), we will use generalised estimating equations for comparisons at 12 months (model 1) and 24 months (model 2) between treatment groups. Group and current participation in preinjury sport will be included as fixed factors. We will calculate mean difference and 95% confidence intervals. In model 2, we will include the 12-month values as a covariate.

For adherence, we will compare the median number of rehabilitation sessions completed per person (i) with the physiotherapist, (ii) at home, (iii) at a gymnasium between the treatment groups using generalised estimating equations.

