## Methods

The BANG trial is a parallel-group, two-arm, superiority trial. Participants with ACL reconstruction will be recruited from one of six clinical sites and randomly allocated (in blocks of 6 with a 1:1 allocation, stratified for site) to receive either usual rehabilitation care alone (control group) or usual rehabilitation care plus the Back in the Game smartphone application (experimental group) (Fig. 1). The primary outcome is return to the preinjury sport and level at 12 months after surgery.

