Limb symmetry index is calculated using the formula: $$ \frac{involved\ limb}{uninvolved\ limb}\times 100 $$; ACL, anterior cruciate ligament

**Table 3 Tab3:** Baseline participant characteristics

Variable	Aggregation
Time from injury to surgery	median (IQR)
Age at injury	mean (SD)
Sex	
Female	n (%)
Male	n (%)
Primary occupation	
Student	n (%)
Desk work	n (%)
Manual work	n (%)
Heavy manual work (e.g. construction)	n (%)
Unemployed	n (%)
Preinjury sports participation	
Contact, pivoting sport	n (%)
Non-contact, pivoting sport	n (%)
Return to sport goal	
Return to same sport	n (%)
Return to different sport	n (%)
Return to sport expectations	
Within 1 month	n (%)
Within 6 months	n (%)
Within 12 months	n (%)
After 12 months	n (%)
IKDC subjective knee form [28] score	mean (SD)
General Self-efficacy Scale [33] score	mean (SD)
Knee Self-Efficacy Scale [25] *Future domain*	mean (SD)
Hospital Anxiety & Depression Scale [34] score	mean (SD)

*IQR* interquartile range, *SD* standard deviation, *IKDC* International Knee Documentation Committee

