### Data collection

All participants download the Back in the Game app, which is how we deliver the intervention, and administer all research data collection. Participants in the experimental group have access to a separate part of the app that only goes ‘live’ when the intervention commences. Participants in the control group cannot see the ‘hidden’ intervention part of the app.

Baseline measurements are collected prior to allocation. Participants complete the baseline questionnaire in the week prior to ACL reconstruction surgery, providing demographic information, sports participation, and a baseline measure of self-reported knee function, self-efficacy, and anxiety and depression (Table 3). The Internet-delivered intervention commences in the first post-operative week (Table 4). Permissions to access the intervention can only be assigned at the time the participant sets up their own profile in the app and provides informed consent.

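### The K-SES and ACL-QoL models omit the randomisation stratum, and the K-SES models omit the collected baseline score, which gives up some precision

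*Protocol article*

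**What the plan says.** All references are to the protocol article.

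- **Design.** The opening of Methods describes allocation "in blocks of 6 with a 1:1 allocation, stratified for site". The sequence-generation section confirms a separate schedule for each site.
- **Primary analysis.** "Group and clinical site will be included as fixed factors in the model".
- **Time-varying secondary analyses** (ACL-RSI, motivation, SANE, IKDC, sports participation, new knee injury). "Group, clinical site, and assessment time point will be included as fixed factors", and "If baseline values were collected, we will also include the baseline value in the relevant model as a covariate". K-SES and ACL-QoL are not among the outcomes listed there.
- **Cross-sectional secondary analyses** (K-SES and ACL-QoL, model 1 at 12 months and model 2 at 24 months). "Group and current participation in preinjury sport will be included as fixed factors". Then: "In model 2, we will include the 12-month values as a covariate".
- **Baseline data.** Data collection says that participants provide, in the week before surgery and before allocation, "a baseline measure of self-reported knee function, self-efficacy, and anxiety and depression". Table 3 lists the K-SES future domain among the baseline variables. Table 2 names the same domain as the outcome at 12 and 24 months. Table 3 has no ACL-QoL baseline.

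**The concern.** The protocol states one adjustment rule for its primary and most secondary outcomes (site, plus the baseline value where it exists) and another for K-SES and ACL-QoL, and gives no reason for the difference. Two pre-randomisation variables that are already held go unused: site for both outcomes, and baseline K-SES for K-SES.

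What is at stake is precision. A baseline score on the outcome's own scale usually explains part of the outcome variance, and adjusting for it narrows the confidence interval at no cost in participants. When allocation is balanced within site and site predicts the outcome, a model without site reports a standard error that is somewhat too large.

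**Working it through.** **The plan's own figure.** The protocol gives no power, SD or correlation for K-SES or ACL-QoL. Its only sample-size figure is for the primary outcome: 33% versus 53%, two-sided alpha 0.05, power 80%, 15% drop-out. The pooled two-proportion formula is

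n = [1.960 × √(2 × 0.43 × 0.57) + 0.842 × √(0.33 × 0.67 + 0.53 × 0.47)]² / 0.20²,

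which rounds up to 96 per arm. Multiplying by 1.15 gives 110.4, so 111 per arm and 222 in total, as stated. Dividing by 0.85 gives 113 per arm (226), within 2% of it.

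**Completers.** 111 × 0.85 = 94.35, so about 94 per arm.

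**Baseline K-SES, 12 months.** The reference is a group-only comparison at 80% power. The detectable difference is (1.960 + 0.842) × √(2/94) = 0.409 SD. Adjusting for a baseline with correlation ρ to the outcome multiplies the residual SD by √(1 − ρ²), so

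power = Φ(2.802/√(1 − ρ²) − 1.960).

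| Assumed ρ | SE ratio | Power |
|---|---|---|
| 0.2 | 0.980 | 81.6% |
| 0.3 | 0.954 | 83.6% |
| 0.4 | 0.917 | 86.4% |
| 0.5 | 0.866 | 89.9% |
| 0.6 | 0.800 | 93.8% |

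At ρ = 0.5 the gain in precision equals that of 94/(1 − 0.25) ≈ 125 completers per arm.

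**Site.** With 1:1 allocation balanced within site, the true standard error is √((1 − ICC) × 2/94), while a model without site works with √(2/94). Therefore:

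- actual size without site = 2 × [1 − Φ(1.960/√(1 − ICC))]
- power without site = Φ(0.842/√(1 − ICC))
- power with site = Φ(2.802/√(1 − ICC) − 1.960)

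| Assumed ICC | Actual size of 5% test, site omitted | Power without site | Power with site | Difference (points) |
|---|---|---|---|---|
| 0.01 | 4.9% | 80.1% | 80.4% | 0.3 |
| 0.02 | 4.8% | 80.2% | 80.8% | 0.6 |
| 0.05 | 4.4% | 80.6% | 82.0% | 1.4 |
| 0.10 | 3.9% | 81.3% | 84.0% | 2.7 |

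**What is not computed.** Model 2 already conditions on the 12-month value, so the gain from baseline K-SES at 24 months is not sized here. For ACL-QoL only the site table applies.

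**The case against.** Several objections carry weight.

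*The power figures are not those of the planned model.* A reader might infer that the planned K-SES test has 80% power and would reach 90% with the baseline score. The documents do not support this. Model 1 also contains current participation in the preinjury sport, which is measured after randomisation and is close to the primary outcome. The figures isolate the value of the baseline term against a group-only comparison. Adding site and baseline would leave the effect of the participation term untouched. This objection stands, and it limits what the figures can be used for.

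*The correlation is unknown.* Baseline is taken in the week before surgery and the outcome a year later, after reconstruction and rehabilitation, so a low correlation is plausible. At 0.2 the gain is only 1.6 points. This stands; the direction is sure for any non-zero correlation, the size is not.

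*The app's direct target.* A reader might infer that the loss falls on the outcome the app most directly aims at. The app addresses confidence, but ACL-RSI measures psychological readiness to return to sport and is at least as direct a target, and its model includes site. Only one of the four K-SES future items asks about regaining the previous activity level.

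*Site matters little.* The protocol's discussion of its pragmatic design expects rehabilitation outcomes to be fairly similar between sites, which points to a small ICC. The protocol also does not name the clustering unit of the estimating equations; if it were site, the standard error might partly reflect it. Both points stand, so site is mainly a matter of consistency.

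*Baseline imbalance is already covered.* The statistical analysis section allows regression adjustment if the groups differ markedly at baseline. That is conditional on the observed data, has no stated threshold, recovers no precision when the groups are balanced, and does not bring in site. It does not replace prespecified adjustment.

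*A full analysis plan may say more.* It may, but the article is not silent here: it names the model terms, and names them differently from the two sections just before.

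**Conclusion.** The point holds as a modest, avoidable loss of precision in two secondary outcomes. The stated K-SES and ACL-QoL models omit the stratification factor, and the K-SES models omit a baseline score held on the same scale, against the rule that the protocol applies elsewhere.

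The textual omission is certain. Its size is not: for K-SES at 12 months it is roughly 2 to 14 power points from an 80% group-only reference, for assumed correlations of 0.2 to 0.6. For site it is 0.3 to 2.7 points for an assumed ICC of 0.01 to 0.10, with a slightly conservative test. For ACL-QoL only the small site effect applies.

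A reader might also infer that the omission makes the comparison biased or invalid. It does not: in a comparison of randomised groups that conditions on nothing measured afterwards, leaving out baseline covariates neither biases a mean difference nor inflates the type I error. The primary analysis, which includes site, is unaffected.

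**What to change.** In the cross-sectional analysis section, add clinical site, as used in the randomisation, to the K-SES and ACL-QoL models, and add the baseline K-SES future score to the K-SES models at 12 and 24 months. This follows the rule already stated for the time-varying outcomes. ACL-QoL has no baseline of its own, so site is the only addition there.

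This change only adds terms. Whether current participation and the 12-month value, both measured after randomisation, should remain in these models is a separate question, to be argued and decided explicitly. Adding site and baseline does not settle it.

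The cost is about one sentence of analysis wording, to be fixed before unblinding. No new data, participants or procedures are needed.

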### Aims and hypothesis

The primary aim of this randomised controlled trial is to test whether Internet-delivered cognitive-behavioural therapy to address confidence for returning to sport (Back in the Game app), is effective for improving the number of people who return to their preinjury sport and level following ACL reconstruction.

The secondary aims are to assess the effect of the Back in the Game app on participation in sport, incidence of new knee injuries, psychological readiness to return to sport, knee self-efficacy, motivation to return to sport, knee-related quality of life, and self-reported knee function.

Our hypothesis is that more patients who use the app in addition to receiving usual rehabilitation care following ACL reconstruction will return to their preinjury sport and level than patients who receive usual care alone.

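### The K-SES and ACL-QoL models adjust for post-randomisation variables that the app can change, so the group coefficient is not the app's total effect on these two secondary outcomes

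*Protocol article*

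**What the plan says.** In the protocol article, under Planned secondary analyses: cross sectional analyses, K-SES and ACL-QoL are analysed by generalised estimating equations for "comparisons at 12 months (model 1) and 24 months (model 2) between treatment groups". The covariates follow: "Group and current participation in preinjury sport will be included as fixed factors". The effect measure is plain: "We will calculate mean difference and 95% confidence intervals". For the later time point: "In model 2, we will include the 12-month values as a covariate".

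Under Aims and hypothesis: "The secondary aims are to assess the effect of the Back in the Game app on participation in sport", and that list goes on to name knee self-efficacy and knee-related quality of life. The same section hypothesises that more app users will go back to their earlier sport and level. Under Methods: "The primary outcome is return to the preinjury sport and level at 12 months after surgery".

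The neighbouring models are built differently. The primary model has group and clinical site. The time-varying models have group, site and time point, and: "If baseline values were collected, we will also include the baseline value in the relevant model as a covariate". The future domain of the K-SES is collected at baseline (Table 3); Table 3 lists no baseline ACL-QoL.

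**The concern.** Current participation is observed after allocation and is something the app is meant to change. Holding it fixed blocks whatever part of the benefit reaches self-efficacy or quality of life through being back in sport. It also compares unlike people. If the app brings back athletes who would otherwise have stayed away, participants in the two arms differ in underlying confidence, and so do non-participants. The protocol's Background and Discussion name confidence and fear as drivers of return to sport, so such a common cause of participation and score is likely.

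The 12-month score in model 2 raises the same issue: it may already carry the effect of the app, and adjusting for it leaves mainly what was gained afterwards.

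At stake are two stated secondary aims. A reader would take the reported mean difference as the effect of the app on these scores, when it answers a different, unlabelled question.

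**Working it through.** **Covariates side by side (besides group)**

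| Model | Covariates | Any post-randomisation? |
|---|---|---|
| Primary | site | no |
| Time-varying | site, time point, baseline value where collected | no |
| K-SES / ACL-QoL, model 1 | current participation | yes |
| K-SES / ACL-QoL, model 2 | current participation, 12-month score | yes, both |

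**Inputs.** The Sample size calculation gives a control rate of 33% and a difference of 20 points, hence 53%. The usual two-proportion formula (two-sided alpha 0.05, power 0.80) gives 96 per arm. Then 96 × 1.15 = 110.4, rounded up to 111, or 222 in total, which is the stated figure. So 33% and 53% are the design rates. The protocol states no SD, effect or correlation for K-SES or ACL-QoL; every such value below is an assumption.

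**Model 1, effect through participation.** Let *gap* be the difference in score produced by participating and *d* the app's direct effect. The total effect is d + (0.53 - 0.33) × gap = d + 0.20 × gap. With no common cause of participation and score, the planned model returns d. In SD units:

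| gap | d | total | planned model | share kept |
|---|---|---|---|---|
| 0.5 | 0 | 0.10 | 0 | 0% |
| 1.0 | 0 | 0.20 | 0 | 0% |
| 1.5 | 0 | 0.30 | 0 | 0% |
| 0.5 | 0.2 | 0.30 | 0.20 | 67% |
| 1.0 | 0.2 | 0.40 | 0.20 | 50% |
| 1.5 | 0.2 | 0.50 | 0.20 | 40% |

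On the 0-100 ACL-QoL, an assumed 15-point gap means 0.20 × 15 = 3 points taken out.

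**Model 1, unmeasured confidence.** Let c be the within-arm correlation between the liability to participate and the rest of the score (normal liability). The model then overstates the participation gap by

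c × SD × [φ(z at 0.33) + φ(z at 0.53)] / (0.33 × 0.67 + 0.53 × 0.47) = c × SD × (0.362 + 0.398) / 0.4702 = 1.616 × c × SD.

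The group coefficient becomes d - 0.20 × 1.616 × c × SD = d - 0.323 × c × SD.

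- A trait loading 0.7 on both gives c = 0.49. The coefficient is -0.16 SD at d = 0 and 0.2 - 0.16 = 0.04 SD at d = 0.2. A simulation with 1,000,000 records gave the same -0.16 and 0.04.
- Loadings of 0.3 to 0.5 give c = 0.09 to 0.25. With SD 15 to 20 and d = 0, the coefficient runs from -0.323 × 0.09 × 15 = -0.4 to -0.323 × 0.25 × 20 = -1.6 points. The total is 3.0 for a 15-point gap.
- The same settings with d = 3 points give about 2.6 down to 1.4, against a total of 6.0.

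**Model 2, 12-month score alone.** With equal SDs, the slope on the 12-month score is rho. If the true difference D is the same at both times, the coefficient is D - rho × D = (1 - rho) × D. For D = 0.40 SD and rho of 0.4, 0.6 and 0.8, this gives 0.24, 0.16 and 0.08 SD; simulation agrees. At rho 0.6 to 0.7, 40% down to 30% is kept. Model 2 as written carries both covariates; the two losses were worked out separately.

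**The case against.** Several counter-arguments carry weight.

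- **Only two secondary outcomes are touched.** The primary model and the time-varying models, including psychological readiness (ACL-RSI), have no such covariate. Table 2 also plans mean or median scores for K-SES and ACL-QoL, so unadjusted summaries will exist. This stands and lowers the severity. The planned inferential comparison is still the adjusted one.
- **The effect is not necessarily removed.** A reader might infer that these models wipe out the effect, or turn a benefit into harm. Complete removal needs the whole effect to run through participation. Table 1 gives a rationale in which the app supports psychological readiness itself, and the K-SES future domain measures confidence about the knee, so a zero direct effect is least plausible for that scale. A wrong sign is possible but needs a small direct effect and a common cause.
- **Participation is not the primary outcome under another name.** The Primary outcome measure section requires four answers: same sport, same level, full training, and modified or full competition. The covariate mentions neither level nor competition, and in model 2 it presumably refers to 24 months. It overlaps closely; applying 33% and 53% to it is an assumption.
- **Adjusting for the 12-month value can answer a fair question** about change from 12 to 24 months. It can, but the text announces a between-group comparison at 24 months and does not label it as change. The (1 - rho) result also needs equal effects and equal variances at both times.
- **Leaving out site and baseline K-SES does not bias a randomised comparison.** Agreed; this affects precision only.
- **The corrected model may not reach significance either.** With 111 × 0.85 = 94 per arm and SD 15 to 20, power for a true 3-point effect is about 18-28%. True, but the estimate and interval would then concern the stated question.

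**Conclusion.** The point holds for two secondary outcomes. As written, the group coefficient in both models is not the total effect of the app on K-SES or ACL-QoL, and nothing in the protocol presents these as mediation or change analyses. The protocol fixes these covariates itself, so this is not a detail left to a later analysis plan.

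Model 1 takes out the part that runs through participation, 0.20 times the gap at the design rates, and can bias what remains. Model 2 keeps (1 - rho) of a sustained, equal effect on account of the 12-month score alone. These sizes rest on assumed gaps, SDs and correlations and on 33% against 53% for the covariate. The documents do not support saying that the effect is wholly removed or that its sign will be reversed.

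The change should be made, but the trial's main conclusion does not depend on it: the primary analysis and the 222 participants are unaffected.

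**What to change.** For the main comparisons of K-SES and ACL-QoL, at 12 months and again at 24 months, fit group and clinical site. Add the baseline K-SES value in the K-SES models only, since Table 3 lists no baseline ACL-QoL. Leave out current participation and the 12-month score. This brings the section into line with the primary and time-varying models.

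If the investigators want to know how much of an effect runs through return to sport, or what changes between 12 and 24 months, the models with those covariates can stay as labelled exploratory mediation or change analyses, with the assumption of no unmeasured common cause stated for the mediation analysis.

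Adding site and baseline K-SES is a smaller gain in precision. A baseline correlation r cuts the residual variance by r squared, that is 9% at r = 0.3 and 25% at r = 0.5 (assumed values).

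The cost is a change of wording in one section, with every variable already collected. It should be made and dated before the analysis is unblinded.
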